Although various predisposing factors have been identified in both conditions, 50–60% of all cases remain unexplained. A potential causative role of inherited (the Factor V Leiden or the prothrombin A20210 gene variants, protein C, protein S or antithrombin deficiency) or acquired (antiphospholipid-antibody syndrome) thrombophilias has been documented [4–6], presumably due to the obstruction in placental vessels caused by haemostatic disorders. Thus, the potential benefit of a prophylaxis with low-molecular-weight heparins (LMWHs) in improving the live birth rate or outcomes in ART procedures has been often investigated and demonstrated by several studies, that are mostly limited by their observational nature or the limited sample size [7–12]. On the contrary, randomized clinical trials (RCTs) on this issue have shown inconclusive results, probably due to heterogeneity and, sometimes, small number of women included [13–18]. Therefore, despite increasing knowledge on reproductive failures over the past decades, there are still several aspects of clinical management, treatment and prognosis with uncertainties that need to be addressed. As far as ART, the need for further well-designed RCTs with larger sample size has also been raised by the last Cochrane review [19]. Unfortunately, RCTs in pregnant/infertile women are often stopped before completing, due to poor and slow recruitment.

To cover these unmet needs and to have further data mainly based on the real-life clinical management, we are currently conducting the OTTILIA (Observational sTudy on antiThrombotic prevention in thrombophILIA and pregnancy loss – NCT 02385461) and FIRST (recurrent Failures in assIsted Reproductive Techniques – NCT 02685800) registries, respectively.

We summarize here the design of these studies and discuss the importance of their results in the clinical practice.

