### Study procedure

All enrolled women are observed from their first visit after positive pregnancy test (OTTILIA) or before commencing a new ART cycle (FIRST) until the end of pregnancy or ART procedure (negative pregnancy test/end of pregnancy, if successful cycle), respectively.

At baseline, clinical information and index- pregnancy/ART cycle details are obtained from all women by a specially trained staff (Table 2). Data are collected by means of questionnaires and recorded in a web-based database including an electronic form for each woman enrolled. To ensure high quality data, a centralized data management performs quality control and plausibility checks according to predefined procedures. Follow-up data (Table 2) are collected during the three trimesters of pregnancy and in the puerperium period (6 weeks after delivery), at the time of hospital stay, routine clinical follow-up visits or telephone interviews.

**Table 2 Tab2:** Baseline and Follow-up data for evaluation and monitoring of women enrolled in the OTTILIA and FIRST registries

OTTILIA	
Baseline Clinical information: • Maternal age • Body Mass Index • Smoking habit • Reproductive history (previous pregnancies and obstetric complications occurred) • Personal and family history of VTE • Presence of inherited or acquired thrombophilias • Thrombophilic risk factors Index-pregnancy information: • Results of performed imaging tests, (ultrasonography, Doppler ultrasonography) • Invasive prenatal testing (i.e. villous sampling, amniocentesis) • Antithrombotic prophylaxis (brand, doses/day, duration)	Follow-up Pregnancy outcomes: • Live birth (gestational age, delivery mode, sex, birth weight, fetal or maternal hemorrhage) • Obstetric complications (PL, IUFD, gestational hypertension, preeclampsia, HELLP syndrome, SGA newborns, placental abruption) • VTE
FIRST	

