Baseline Clinical information: • Maternal age • Body Mass Index • Smoking habit • Reproductive history (previous spontaneous pregnancies, ART attempts) • Cause of infertility (female, male, mixed or idiophatic), • Personal and family history of VTE • Presence of inherited or acquired thrombophilias • Thrombophilic risk factors Index-ART cycle information: • Fertilization (autologous/heterologous) • Type of ART procedure (IUI, IVF, ICSI, Other) • Ovarian stimulation (brand, doses/day, duration) • Antithrombotic prophylaxis (brand, doses/day, duration), • Number of oocytes retrieved •Number of embryo transfers	Follow-up ART outcomes: • Clinical pregnancy • Live birth (gestational age, delivery mode, sex, birth weight, fetal or maternal hemorrhage) • Obstetric complications (PL, IUFD, gestational hypertension, preeclampsia, HELLP syndrome, SGA newborns, placental abruption) • OHSS (time of occurrence after ovarian stimulation, severity, estradiol levels pg/ml, treatment) • VTE

*VTE* venous thromboembolism, *IUI* intrauterine insemination, *IVF* in vitro fertilization, *ICSI* intracytoplasmic sperm injection, *PL* pregnancy loss, *IUFD* intrauterine fetal death, *SGA* small-for-gestational age, *OHSS ovarian hyperstimulation syndrome*

The primary outcome is the live birth rate in the OTTILIA register and live birth or clinical pregnancy rate in the FIRST. The definition of all primary and secondary outcomes is provided in Table 3.

**Table 3 Tab3:** Definitions of primary and secondary outcomes in the OTTILIA and FIRST registries

	Definitions	Source
Clinical pregnancy	A pregnancy confirmed by ultrasonographic visualization of gestational sac or fetal heartbeat	Wang X et al. Fertil Steril 2003; 79: 577–9.
Live birth	The delivery of a live newborn	https://www.gfmer.ch/Medical_education_En/Live_birth_definition.htm
Pregnancy loss (PL)	A loss occurring ≤20 weeks	Regan L. BMJ 1991; 302: 543–4
Intrauterine fetal death (IUFD)	A loss occurring after 20 weeks	Royal College of Obstetricians & Gynaecologists. Late intrauterine fetal death and stillbrith (Green-top Guideline 55). London: Royal College of Obstetricians & Gynaecologists; 2010 [cited 2019 May 30]
Preterm birth	The delivery of an infant before completion of 37 weeks gestation	ACOG Committee Opinion No 579: definition of term pregnancy. Obstet Gynecol. 2013;122: 1139–40

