Gestational hypertension (GH)	Blood pressure ≥ 140/90 mmHg after 20 weeks of gestation in a previously normotensive woman	www.nice.org.uk/guidance/cg107
Preeclampsia	Blood pressure ≥ 140/90 mmHg and proteinuria of 0.3 g or more in a 24-h urine specimen occurring after 20 weeks of gestation in a previous normotensive woman	www.nice.org.uk/guidance/cg107
HELLP syndrome	Thrombocytopenia (i.e. platelet count < 150,000 cells/μL), elevated AST and/or ALT (> 40 IU/L), increased LDH (> 600 IU/L), and hemolysis (increased LDH level)	Martin JN et al. Am J Obstet Gynecol 1999; 180: 1373–84.
Small-for-gestational age (SGA) newborns	Apparently healthy neonate with birthweight <10th centile for gestational age in the absence of infection and maternal drug or alcohol abuse	RCOG. The investigation and management of the small–for–gestational–age fetus. Green-top Guideline. 2nd ed.; 2014
Placental abruption	The early separation of the placenta from the uterus	Ananth CV, et al. Am J Obstet Gynecol. 2016;214: 272
Ovarian hyperstimulation syndrome (OHSS)	An exaggerated systemic response to ovarian stimulation with a wide spectrum of clinical and laboratory manifestation. According to the degree of manifestations it is classified as mild, moderate, or severe.	Humaidan P, et al. Hum Reprod. 2016;31: 1997–2004
Venous thromboembolism (VTE)	Deep vein thrombosis (DVT), defined as a blood clot in deep veins of the legs with or without pulmonary embolism (PE). DVT is diagnosed if confirmed by Doppler ultrasound exam. PE diagnosis is confirmed by ventilation-perfusion lung scanning, angiography, or computed tomography. Pregnancy-related VTE is defined as a VTE occurring during the pregnancy or in the puerperium (within 6 weeks after delivery).	Kearon C, et al., Chest 2012; 141 (2 Suppl): e419S-e496S.
Hemorrhage.	Bleeding events. They are classified as major or minor according the ISTH criteria. Wound hematoma in case of caesarean section	Schulman S, J Thromb Haemost 2005; 3: 692–4.

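### Table 3 ties the SGA outcome to an undefined neonatal health status and nests preeclampsia inside gestational hypertension, so both secondary comparisons can mislead

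*Protocol article*

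**What the plan says.** Under Study procedure, the article states: "The definition of all primary and secondary outcomes is provided in Table 3". Table 3 is therefore the working rule and not a summary of one.

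- **SGA newborns:** "Apparently healthy neonate with birthweight <10th centile for gestational age in the absence of infection and maternal drug or alcohol abuse".
- **Gestational hypertension:** "Blood pressure ≥ 140/90 mmHg after 20 weeks of gestation in a previously normotensive woman".
- **Preeclampsia:** "Blood pressure ≥ 140/90 mmHg and proteinuria of 0.3 g or more in a 24-h urine specimen", with the same timing and prior-status condition, "occurring after 20 weeks of gestation in a previous normotensive woman".

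Table 2 lists the complications to be recorded in both registries as separate items, including "gestational hypertension, preeclampsia, HELLP syndrome, SGA newborns, placental abruption". It gives no hierarchy or exclusion between them. For live births it also records gestational age, sex and birth weight.

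The Statistical analysis plan section will compute a relative risk with a 95% confidence interval for outcome occurrence. The first secondary aim is to evaluate obstetric complications by characteristics of the women and by treatment. The Data management section says that subjective reading of outcomes is avoided by well-defined scores.

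**The concern.** **SGA.** Whether a newborn is healthy is known only after exposure to low-molecular-weight heparin. The Background explains the role of thrombophilia as "presumably due to the obstruction in placental vessels caused by haemostatic disorders". Impaired placental supply could plausibly make an infant both small and ill. Counting only the healthy ones screens the outcome on a possible consequence of the process under study. The condition is also undefined. Among the fields shown in Table 2 there is none for neonatal health, infection, or maternal drug or alcohol abuse, so centres would apply the qualifiers by local judgement. That sits badly with the claim made under Data management.

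**Hypertension.** If preeclampsia satisfies the gestational hypertension rule, a relative risk for gestational hypertension mixes two conditions. Centres that code one item and centres that code both would also produce counts that cannot be compared.

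At stake are the size, and possibly the direction, of two comparisons under the first secondary aim.

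**Working it through.** The article gives no rate for SGA, gestational hypertension or preeclampsia, so there is no plan figure to reproduce. The nesting follows from the wording alone. Every rate below is an assumption.

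**1. Nesting.** Take four criteria: blood pressure at or above 140/90, after 20 weeks, previously normotensive, proteinuria. Gestational hypertension needs the first three and preeclampsia needs all four. Of the 16 possible combinations, the one that meets preeclampsia also meets gestational hypertension. The only combination that is gestational hypertension alone is the one without proteinuria.

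**2. Effect on the gestational hypertension relative risk.** Let g be proteinuria-free hypertension, equal in both groups (true RR 1.0), let e be preeclampsia in the untreated, and let r be the preeclampsia RR.

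RR as written = (g + e·r) / (g + e)

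With g = 6%, e = 4% and r = 0.5: (6 + 2) / (6 + 4) = 0.80.

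| e | r = 0.5 | r = 0.7 |
|---|---|---|
| 2% | 7.0/8 = 0.88 | 7.4/8 = 0.93 |
| 4% | 8.0/10 = 0.80 | 8.8/10 = 0.88 |
| 6% | 9.0/12 = 0.75 | 10.2/12 = 0.85 |
| 8% | 10.0/14 = 0.71 | 11.6/14 = 0.83 |

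Across this range the overlap alone turns a null result into 0.71 to 0.93.

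**3. Effect on the SGA relative risk, literal reading.** Let R be the true RR for birthweight below the 10th centile. Let q0 and q1 be the shares of those infants who are ill, untreated and treated.

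Recorded RR = R × (1 − q1) / (1 − q0)

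With R = 0.80 and treatment halving the ill share (q1 = q0/2):

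- q0 = 10%: 0.80 × 0.95/0.90 = 0.84
- q0 = 20%: 0.80 × 0.90/0.80 = 0.90
- q0 = one third: 0.80 × (5/6)/(2/3) = 1.00
- q0 = 40%: 0.80 × 0.80/0.60 = 1.07

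Under halving, the direction reverses when q0 > (1 − R)/(1 − R/2). For R = 0.80 this is 0.20/0.60, or one third. For R = 0.95 it is 0.05/0.525, or about 9.5%. As an example of the latter, take 12% small with 30% ill, against 11.4% small with 15% ill. The recorded rates are 0.12 × 0.70 = 8.4% and 0.114 × 0.85 = 9.7%, an RR of about 1.15 against a true 0.95.

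If instead treatment acts only by halving the number of ill small infants, the true RR is 1 − q0/2. That is 0.95 to 0.80 for q0 of 10–40%, and the recorded RR is 1.0 throughout.

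**The case against.** - **The SGA wording may exclude by cause.** The same sentence goes on to rule out infection and maternal substance abuse. A centre could read *apparently healthy* as free of malformation or other non-placental cause, which would sharpen the outcome. This stands against the stronger inference that the most severe growth restriction is certainly dropped. It does not rescue the definition: a term open to both readings will be applied differently across centres.
- **Stillborn infants are not lost.** A reader might infer that they vanish from the data. Table 3 makes intrauterine fetal death an outcome of its own, and such a death is also a failure of live birth, OTTILIA's primary outcome. This stands. An outcome about newborns may reasonably be limited to live births.
- **Double counting is not planned.** A reader might infer that events will be summed across complications. The article describes no such total or composite. This stands.
- **A reversed sign needs particular inputs.** At a true RR of 0.80 with the ill share halved, more than a third of untreated small infants would have to be ill; smaller shares only attenuate. This stands for that case. The threshold falls as the true RR nears 1, so reversal cannot be ruled out, but nothing in the article makes it the expected result.
- **The data allow repair.** Birth weight, gestational age and sex are recorded for live births, and the two hypertensive items are separate. This is true, and it makes the fix cheap. But Table 3 prescribes the narrower SGA count, and changing it after results are seen would be post hoc.

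**Conclusion.** The point holds for two definitions that the article itself fixes. The nesting of preeclampsia within gestational hypertension is certain from the text, and no other section separates them. The SGA restriction holds on a literal reading; on a narrower reading the outcome is ambiguous rather than truncated, and still needs correcting.

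The size depends on assumed rates. For gestational hypertension, a true RR of 1.0 becomes 0.80 in the central example and 0.71 to 0.93 over the range tried. For SGA, the likeliest harm is attenuation towards 1.0. A change of direction needs stronger assumptions, chiefly that treatment makes small infants healthier while changing their number relatively little.

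The documents do not support saying that the worst cases are known to be removed or that the SGA result will come out backwards. Only secondary outcomes are affected; neither definition enters the primary outcomes or the sample sizes.

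**What to change.** **SGA.** Define it as birthweight below the 10th centile for gestational age in all live births, derived centrally from the birth weight, gestational age and sex already collected. Apply the health, infection and substance-use exclusions only in a sensitivity analysis, and say what *apparently healthy* means there. If centres have coded SGA by the present rule, that item could serve for the sensitivity analysis.

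**Hypertension.** For analysis, count gestational hypertension only in women without proteinuria, that is, without recorded preeclampsia. Alternatively, report one line for any hypertensive disorder with preeclampsia as a subset.

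**Cost.** Two definitions are reworded and two variables derived, with no new data for the main analyses. The change should be dated and made before outcomes are compared by treatment.

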### Data management

Data are stored and analysed in a central database. Access to the study documentation system and the study database requires user authentication and is restricted to the responsible study staff. Women are consecutively enrolled, so avoiding possible errors deriving from subject selection. Further errors deriving from a subjective interpretation of outcome measurements are avoided through using well-defined scores. Also, standardization of collection procedure has been thought to avoid errors due to data collection.

### Statistical analysis plan

Absolute numbers, percentage and median (range) or mean (±standard deviation) will be calculated to describe study groups and sub-groups. Associations between aforementioned primary and secondary outcomes and both numerical and categorical variables (age, drugs, co-morbidities, medical procedures, drug regimens and doses, etc.) collected during study will be tested. Relative risk value, with a 95% confidence interval, will be computed for the comparison of outcomes occurrence.

Validity of primary results will be examined, using a sensitivity analysis of sub-groups and applying more than one statistical test. Parametric and non-parametric statistical tests, according to data distributions, will be used for comparison of categorical and numerical variables. Strategy to prevent missing data will be employed. We select clinical information and laboratory measurements that are routinely included in the ‘real word’ practice, to facilitate the adherence of the investigators to the study protocol. Contacts will be kept with the investigators to reduce the burden of missing data as much as possible. A query-based system will allow us to ask investigators for the missing variables, whether the variables are meaningful for the final analysis. A *p* value below 0.05 will be considered to define statistical significance.

Stratification according to sub-groups of subjects will be taken into account on the basis of propensity to receive or not the treatment. This strategy will allow for an accurate and statistically valid analysis of heterogeneity that will be eventually observed. Potential confounding factors will be identified and after the evaluation of possible relationship between single variables by univariate analysis, logistic regression analysis will be performed to estimate the independence of associations identified. Data analysis will be performed also taking into account type of molecules administered, starting time and duration of thromboprohylaxis.

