### Participants

All consecutive women who meet the inclusion criteria for the OTTILIA or FIRST registries (Table 1) are recruited by participating Centers on admission after obtaining informed consent. Women eligible for the OTTILIA register can undergo thrombophilia test before conception, according to local policy. If the test is not available or the test was not prescribed by the physician, women included are considered as non- carriers. As far as FIRST, knowledge of thrombophilia status is not a prerogative of the register. However, when information is available, it will be considered in final analysis.

**Table 1 Tab1:** Inclusion and exclusion criteria of the OTTILIA and FIRST registries

OTTILIA	FIRST
Inclusion criteria	
• Pregnancy confirmed by urine/blood pregnancy test or ultrasound examination • Previous recurrent otherwise unexplained PL * ≥3 or 2 PL in the presence of at least 1 normal fetal karyotype* or • At least 1 previous IUFD * A loss after 20 weeks of a morphologically normal fetus*	• ART cycle at enrolment *First, second and third level ART cycles* • 2 or more implantation failures/losses of clinical pregnancies after ART (independently of the number of embryos transferred) *At least 2 previous cycles with negative pregnancy test and/or PL after a positive pregnancy test*
Exclusion criteria	
• Personal history of venous and/or arterial thromboembolism • Allergy to LMWHs • Uterine abnormalities • Cervical incompetence • Chromosomal abnormalities in parents • Known hemorrhagic diathesis	• Uterine abnormalities • Hydrosalpinx • Chromosomal abnormalities in parents • Known hemorrhagic diathesis • Previous inclusion in the study

*PL* pregnancy loss, *IUFD* intrauterine fetal death, *ART* assisted reproductive technologies, *LMWHs* low-molecular-weight heparins

Enrolled women are free to withdraw their informed consent and exit from the study.

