### Study size estimation

In the literature, the likelihood of observing live births without any treatment is estimated to range between 55 and 80% [2]; a multicentre Italian study [9] showed the occurrence of complications in 50% of all untreated women during pregnancy. Given these estimates, for the OTTILIA register, in order to observe an absolute increase of 15–20% (statistical power: 80%, significance level: 0.05), we calculated the inclusion of 190–340 thrombophilic women and, simultaneously, a cohort of pregnant women with the same clinical history (see inclusion criteria) not carrying inherited thrombophilia, in a ratio of at least 1:1. Thus, an overall number of 380–680 consecutive pregnancies are needed.

As far as the FIRST register is concerned, we estimated the inclusion of 624 women. This estimate is calculated on the basis of (1) the probability of observing live births after ART procedures (20–30%), (2) the estimate of an absolute increase of 5–10% in the number of live births after a prophylaxis of LMWHs (statistical power: 80%, significance level: 0.05).

It has been estimated that the OTTILIA and FIRST registries will be executed in the periods February 2012–December 2020 and October 2015–September 2020, respectively. In both the registries, an additional period of 9 months from the date of the last enrollment will be considered.

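### The confounder set rests on one-at-a-time screening, and the logistic adjustment is not tied to the declared relative risk

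*Protocol article*

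**What the plan says.** All of the analysis text is in the Statistical analysis plan section of the Protocol article.

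- Effect measure: "Relative risk value, with a 95% confidence interval, will be computed for the comparison of outcomes occurrence".
- Regression: potential confounders are to be identified, and "after the evaluation of possible relationship between single variables by univariate analysis, logistic regression analysis will be performed". Its purpose is "to estimate the independence of associations identified".
- Other control of confounding: "Stratification according to sub-groups of subjects will be taken into account on the basis of propensity to receive or not the treatment". The next sentence presents this as a way to analyse heterogeneity.
- Significance: a p "value below 0.05 will be considered to define statistical significance".

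The section sets no p-value for the univariate step, does not say that variables failing it are excluded, and does not mention odds ratios.

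The section Design and setting of the study says that treatment, including LMWH, is left to current practice. The Aims section makes a possible benefit of LMWH part of a primary aim.

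**The concern.** The LMWH comparison is not randomised, so its credibility depends on how confounders are chosen and how the adjusted effect is expressed. Both are weakly fixed.

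**Choice of confounders.** If women at higher risk are treated more often and treatment helps, a risk factor's crude association with live birth is pulled towards nothing. Judging variables singly can therefore discard the ones that matter most under confounding by indication. The text offers no other basis for choosing what enters the model.

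**Scale.** The declared measure is a relative risk, and the named adjusted model gives an odds ratio directly. If the paper sets a crude relative risk beside an adjusted odds ratio, the reader cannot separate the effect of adjustment from the change of scale.

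**Primary adjustment.** Propensity strata and regression may give different answers, and the plan does not say which one counts.

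**Working it through.** **1. The plan's own figures.** The article gives no adjusted effect to reproduce, only sample sizes. These show that the planned effects are absolute differences in proportions. With n per arm = [1.96√(2p̄(1−p̄)) + 0.842√(p₁(1−p₁)+p₂(1−p₂))]² / (p₂−p₁)², taking two-sided 0.05, 80% power and equal arms:

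- OTTILIA, 50→65%: 170 per arm, 340 in total. 50→70%: 93 per arm, 186 in total. Stated: 190–340. The 50% base matches the Study size estimation section, where an Italian study "showed the occurrence of complications in 50% of all untreated women during pregnancy".
- FIRST, 20→30% with continuity correction: 313 per arm, 626 in total. Stated: 624.

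So the article uses differences for size and relative risk for reporting, and a model whose native scale is the odds ratio for adjustment.

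**2. Gap between the scales.** RR = p₂/p₁ and OR = [p₂/(1−p₂)]/[p₁/(1−p₁)], so OR/RR = (1−p₁)/(1−p₂). Inputs come from Study size estimation: for OTTILIA, "the likelihood of observing live births without any treatment is estimated to range between 55 and 80" per cent with an increase of 15–20 points; for FIRST, 20–30% live births with an increase of 5–10 points.

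| Registry | Change | RR | OR | OR/RR |
|---|---|---|---|---|
| OTTILIA | 50→65% | 1.30 | 1.86 | 1.43 |
| OTTILIA | 55→70% | 1.27 | 1.91 | 1.50 |
| OTTILIA | 65→80% | 1.23 | 2.15 | 1.75 |
| OTTILIA | 80→95% | 1.19 | 4.75 | 4.00 |
| FIRST | 20→25% | 1.25 | 1.33 | 1.07 |
| FIRST | 20→30% | 1.50 | 1.71 | 1.14 |
| FIRST | 30→40% | 1.33 | 1.56 | 1.17 |

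Example, 55→70%: RR = 0.70/0.55 = 1.27; OR = (0.70/0.30)/(0.55/0.45) = 2.333/1.222 = 1.91.

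**3. How screening can lose a confounder.** Every input in this step is an assumption. A binary risk factor C is present in half the women. Of women with C, 75% are treated; of those without, 25%. C has odds ratio 0.58 for live birth and treatment has 2.25. Live birth is 65% in untreated women without C (inside the article's 55–80%).

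- Without C: 0.650 untreated, 0.807 treated. With C: 0.519 untreated, 0.708 treated. C therefore lowers live birth by 13 points in untreated and 10 points in treated women.
- Crude rate without C: 0.75×0.650 + 0.25×0.807 = 0.689. With C: 0.25×0.519 + 0.75×0.708 = 0.661. The crude difference is only 0.029.
- At 380 women (190 per level), SE = √[(0.689×0.311 + 0.661×0.339)/190] = 0.048 and z = 0.60, so p exceeds 0.05 about 91% of the time. At 680 (340 per level), z = 0.80 and about 87%.
- If C is left out, treated women have 0.75×0.708 + 0.25×0.807 = 0.733 and untreated women 0.25×0.519 + 0.75×0.650 = 0.617. The treatment odds ratio is (0.733/0.267)/(0.617/0.383) = 1.70 instead of 2.25.

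A simulation with the same confounder, treatment shares and effects, screening at p<0.05, agrees. C was dropped in 89% of runs at 380 and 86% at 680. The mean treatment odds ratio was 1.79 after screening, against 2.28 and 2.25 with full adjustment.

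**4. Both problems together.** In the same example the crude relative risk is 0.733/0.617 = 1.19. The relative risk standardised to the whole sample is (0.807+0.708)/(0.650+0.519) = 1.30. The adjusted odds ratio is 2.25. A reader shown 1.19 and then 2.25 would credit adjustment with a change that is mostly one of scale.

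**The case against.** The article never says that odds ratios will be reported. It names relative risk, and it gives regression the limited task of checking whether associations are independent. A logistic model can be standardised to a relative risk. An odds ratio is a different measure and not a biased one; it overstates only if read as a relative risk. All of this stands. A reader might infer that the registries will publish inflated effects, but the text does not support that.

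Exclusion of variables after the univariate step is also an inference. It is the natural reading, since the model is to examine associations already identified, but it is not written.

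Regression is not the only adjustment: propensity stratification is planned in the same paragraph. That weakens any claim that treatment and indication are separated by regression alone. It does not settle the matter, because the article ties the strata to heterogeneity and ranks neither method.

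Two further readings are tempting. One is that centre is wrongly omitted, because in OTTILIA women "can undergo thrombophilia test before conception, according to local policy". That phrase concerns testing, not treatment, and a centre term is detail that a fuller plan may hold. The other is that items such as oocytes retrieved or Doppler results will be adjusted for. They are listed for data collection, and nothing places them in a treatment model.

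Finally, 80→95% is an extreme corner of the range, and the stated OTTILIA sizes fit a 50% base better. The gap there is still 1.30 against 1.86.

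**Conclusion.** The point holds as one about method and clarity. The article declares a relative risk, points to univariate results as the route into a logistic model, and gives no way back to an adjusted relative risk. It also leaves open which adjustment is primary.

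Size: for a 15-point gain across OTTILIA's 55–80% range, the odds ratio is 1.5 to 4.0 times the relative risk. For FIRST, at the live-birth rates and gains tabulated above, the factor is 1.07 to 1.17, so the scale problem is mainly OTTILIA's. The screening problem applies to both registries. Its size cannot be derived from the article; the 86–89% figure depends on the assumed confounder, treatment shares and p<0.05 screen. In that example screening hid benefit. With other patterns of treatment it could exaggerate it.

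The documents do not show that an overstated effect will be reported, and no sample size is affected. The change should be made because a clearly better method is available with data already being collected.

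**What to change.** For the LMWH comparison, state the following.

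1. **Confounders.** Enter a clinically pre-specified set of pre-treatment variables from Table 2, whatever their univariate p-values: maternal age, body mass index, smoking, reproductive history, known thrombophilia status and family history of VTE. For FIRST add personal history of VTE, cause of infertility, type of ART procedure and fertilisation source. Personal thromboembolism is an exclusion criterion in OTTILIA, so it has no role there. Univariate tables can stay as description.
2. **One primary adjustment.** Use the same set in the propensity model. Name either the propensity analysis or the outcome regression as primary and the other as a sensitivity analysis.
3. **One scale.** Report the adjusted effect as a relative risk and a risk difference with 95% confidence intervals, from modified Poisson regression with robust variance or by standardisation from the logistic model. If an odds ratio is also shown, label it as such and do not set it against the crude relative risk.

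Cost: a change of analysis wording, slightly more analysis work and a few more model degrees of freedom. No new data are needed.
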